### 2.6. Data Collection

All data needed for the analysis, meaning outcome measures, socio-demographic data, and assessment evaluations, will be computed pseudonymized in a different Excel file, secured by the research network. Information will be collected from nurses’ Excel charts and databases already in use by the pharmacy service and hospital facilities. The region shares an integrated electronic database that provides access to data from all surrounding facilities. Data collection will be carried out for the primary outcome over 12 months before and over 12 months after enrollment, and for secondary outcomes through 6 and 12 months following enrollment (Table 1). Specifically, questionnaires on self-care and the quality of received care will be administered at three time points: enrolment, 6 months, and 12 months. To establish the correlation between hospitalization and patients’ underlying chronic diseases, hospital discharge records, IDC codes, and discharge summaries will be assessed. When ICD codes do not specifically refer to “exacerbation” or “acute on chronic” or “decompensated” condition, the discharge letters will be analyzed, searching for the same information. When these criteria are not met, hospitalization will be considered generic, and two GPs will be involved to assess the correlation; any disagreement will be resolved through discussion.

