
### 2.5. Outcomes

The primary clinical outcome will be a composite of at least one event, including emergency department visits or hospitalization for related pathological causes. This outcome will be evaluated pre- and post-intervention to assess the effectiveness of the proactive care on hard endpoints. On the other hand, secondary outcomes will be assessed after the intervention in terms of the following:Medication adherence through the calculation of the periods elapsed between prescriptions;Self-care ability assessed using the Patient Activation Measure (PAM) [41];Quality of received care by Patient-Reported Experience Measurement (PREMsT questionnaire).

The following process evaluations will also be collected during the reference period:Number of patients with periodic use of the nursing service (at least three visits);Number of nursing visits for each user;Number of nurse visits at home;Number of users that received structured family assessment interviews;Number of medical visits by the general practitioner for each user;Rate of users with new prescriptions of aids/devices;Number of services activated per person: physiotherapist, palliative care, social worker, etc.;Rate of users reported to the general practitioner for suspected exacerbation of chronic pathology.

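### The relatedness rule for hospitalizations looks for exacerbation wording rather than the reason for admission, and the two GPs see only admissions that lack the wording

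*Protocol article*

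**What the plan says.** Section 2.5 of the protocol article defines the primary outcome as "a composite of at least one event, including emergency department visits or hospitalization for related pathological causes". It is binary per patient and is compared between the 12 months before and the 12 months after enrollment.

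Section 2.6 gives the working rule for hospitalizations. Its stated aim is "To establish the correlation between hospitalization and patients’ underlying chronic diseases". The rule then runs in order:

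1. **Codes.** The next step applies "When ICD codes do not specifically refer to" an exacerbation, an acute-on-chronic or a decompensated condition. No diagnosis position, principal or secondary, is named.
2. **Letters.** In that case "the discharge letters will be analyzed, searching for the same information. When these criteria are not met, hospitalization will be considered generic". No part of the letter is named, and the reason for admission is not separated from complications or history.
3. **GPs.** Two GPs then assess whether a generic admission is related. Disagreement is settled by discussion.

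No further step is given for an admission that meets the criterion at step 1 or 2.

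**The concern.** Section 2.5 sets a test of cause, whereas the criterion in section 2.6 is a test of wording. The two can disagree when a patient is admitted for something else and the codes or letter also mention a worsened chronic disease. Examples are a hip fracture followed by a COPD exacerbation on the ward, entered as a secondary code, or an elective admission whose letter lists an earlier decompensation.

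The safeguard works in one direction only. GP review can recover related admissions that lack the wording, but it cannot remove unrelated admissions that carry it. Because the outcome is at least one event per window, a single false match makes a patient positive for a full 12 months. Section 3 says the results will be discussed mainly through the observed effect size, so dilution of that effect bears directly on what the study will report.

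**Working it through.** **Text check.** The rule was followed for three kinds of admission.

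| Admission | Cause test (2.5) | Wording test (2.6) | Seen by GPs? |
|---|---|---|---|
| Exacerbation is the reason for admission and is worded so | related | met | no, and none needed |
| Related cause, wording absent | related | not met | yes |
| Other cause, wording only in a secondary code, complication or history | not related | met on the natural reading | no |

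The third row is the gap.

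**Size.** The plan states no event rates, so it has no figure to reproduce. The rates below are assumptions that show direction and order of magnitude only.

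Let p1 and p2 be the true shares of patients with an event before and after, and let f be the share of otherwise event-free patients made positive by a false match, equal in both windows. Then:

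- observed pre = p1 + (1 − p1)f
- observed post = p2 + (1 − p2)f
- observed difference = (p1 − p2)(1 − f)

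*Ratio scale.* Assume 110 patients (the middle of the 100–120 target), p1 = 25% and p2 = 17.5% (ratio 0.70). Assume also that 10–20% of the remaining patients have only unrelated admissions, and that 20–40% of those carry the wording. Then f runs from 0.10 × 0.20 = 0.02 to 0.20 × 0.40 = 0.08.

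- False positives before enrollment: 0.75 × 0.02 = 1.5 points to 0.75 × 0.08 = 6.0 points, which is 1.7 to 6.6 of 110 patients.
- Observed ratio at f = 0.02: (0.175 + 0.825 × 0.02)/(0.25 + 0.75 × 0.02) = 0.1915/0.265 = 0.723.
- Observed ratio at f = 0.08: (0.175 + 0.825 × 0.08)/(0.25 + 0.75 × 0.08) = 0.241/0.310 = 0.777.

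This treats every such patient as having no other event. A patient already positive through an emergency department visit cannot be misclassified again. If half were already positive (again an assumption), f halves to 0.01–0.04:

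- f = 0.01: 0.18325/0.2575 = 0.712
- f = 0.04: 0.208/0.280 = 0.743

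If all were already positive, the ratio stays at 0.70.

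*Difference scale and power.* Assume p1 = 40%, p2 = 25%, within-patient correlation 0.3 and two-sided alpha 0.05. For McNemar's test, with discordant shares p10 and p01, d = p10 − p01 and s = p10 + p01, power ≈ Φ[(d√n − 1.96√s)/√(s − d²)].

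- f = 0: d = 0.150, s = 0.323; at n = 100, (1.5 − 1.113)/0.548 = 0.706, so power is 0.76.
- f = 10%: d = 0.135, s = 0.383; at n = 100, (1.35 − 1.213)/0.604 = 0.227, so power is 0.59.

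| f | Observed difference | Power, n = 100 | Power, n = 120 |
|---|---|---|---|
| 0 | 15.0 points | 0.76 | 0.83 |
| 5% | 14.3 points | 0.67 | 0.75 |
| 10% | 13.5 points | 0.59 | 0.67 |

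**The case against.** The strongest reply is that the steps serve their lead sentence. People assess the codes and analyze the letters in order to link the admission to the patient's underlying diseases, so a sensible reader would not count an old decompensation in the history. An article may also condense a fuller adjudication procedure. Part of this stands. The text does not describe a mechanical keyword match, and automatic acceptance is inferred from the order of steps. Yet the article chose to publish a criterion, a sequence and a referral trigger, and these leave the secondary-code case unreviewed. A fuller manual would still have to depart from these sentences to close the gap.

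A reader might infer three stronger claims, none of which the documents support:

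- **That the rule ignores whose disease it is.** The lead sentence names the patient's own chronic diseases, and acute-on-chronic wording normally implies that the patient has the chronic disease. What is absent is an explicit match to the recorded conditions. There is also no single index disease, since section 2.2 requires at least one non-oncological chronic condition.
- **That unrelated admissions will enter the outcome, and often.** The wording makes this possible. Nothing in the documents shows how often it would happen.
- **That the error biases the result in a chosen direction.** One rule covers both windows, so equal error only dilutes. Directional bias would need recording practice to change between windows, and the documents show no such change.

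It is also fair to say that the shift is small beside sampling error. With 25% and 17.5% in 110 patients, treating the windows as independent, the standard error of the log ratio is √(0.75/27.5 + 0.825/19.25) = 0.265. The 95% interval around 0.70 is then about 0.42 to 1.18. That limits the importance of the point, but it is no reason to keep a rule that does not match the endpoint.

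**Conclusion.** The concern holds as a mismatch between the definition in section 2.5 and the working rule in section 2.6. The wording test does not require the worsened state to be the reason for admission, and admissions that pass it are not sent to the GPs. On the natural reading, some admissions for other causes can therefore count as "emergency department visits or hospitalization for related pathological causes" without review.

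The likely effect is dilution, provided the error is equal in both windows. Its size cannot be known from the documents: the range of 0.72 to 0.78 for a true ratio of 0.70, and the power figures, rest wholly on assumed rates. The effect is smaller or absent for patients already positive through an emergency department visit. This is a cheap improvement to the accuracy of the primary outcome and does not invalidate the design.

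**What to change.** In section 2.6, state that a hospitalization is classified as related without GP review only when the principal diagnosis, or the reason for admission stated in the discharge letter, is an exacerbation, acute-on-chronic or decompensated state of a non-oncological chronic condition recorded for that patient. The diseases collected at the first interview (section 2.4, clinical condition) can serve as the list.

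Send every other admission to the two GPs, including those where the wording appears only in secondary diagnoses, complications or past history. Apply the same rule and the same list to both 12-month windows.

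The cost is about two sentences in the protocol and somewhat more admissions for the two GPs already assigned to this task. No new data source is needed, because discharge records, codes and letters are already to be examined.

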### 2.7. Intervention Fidelity and Contamination

The intervention plans to provide patients with an additional service to the usual care delivered by their primary family and community nurses. For this reason, patients’ study dropout is expected to be low. Instead, the fidelity of the intervention needs to be monitored. A researcher will be responsible for overseeing the monitoring of the entire study process. Participating nurses will record the number, duration, and dates of face-to-face sessions and follow-up phone calls. To ensure adherence to the structured assessment and communication techniques, 15% of sessions will be audiotaped, contingent on participant consent. These will be reviewed using a checklist developed by the research team. The principal investigator will conduct weekly meetings with the intervention nurses to discuss their experiences, address challenges encountered during the delivery session, and provide feedback. In addition, the researcher will review the patients’ Excel files weekly. If deviations from the study protocol are identified, the nurses may be provided with further training.

### 2.8. Statistical Analysis

Sample characteristics will be synthesized after performing descriptive analysis and normality tests. Frequencies and percentages will be used for categorical variables, and means and standard deviations will be used for continuous normally distributed variables. For continuous data exhibiting skewed distributions, medians and interquartile ranges will be computed. The distributions of outcome variables will be assessed, and normalization transformations will be applied where necessary. To compare pre- and post-intervention outcomes, the Wilcoxon signed-rank test and McNemar’s test will be used. Even if the intervention is non-harmful and expectations are for a low-loss follow-up, to assess primary and secondary outcomes at the individual level, researchers will use an intention-to-treat approach. Changes in measures assessed over time will be evaluated using generalized estimating equation (GEE) models, with adjustments for baseline confounders. Statistical significance will be set at *p* < 0.05. Researchers will consider performing sensitivity analysis to enhance the transparency of the results [37]. If an external shock occurs, post hoc sensitivity analysis will be used. All analyses will be performed by the authors using R-4.5.3. and STATA 18 software.

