## 2. Methods

### 2.1. Study Design and Setting

A quasi-experimental pre–post study will be conducted in a Community Health Home in a rural district in the North of Italy with a population of 15,917 citizens, served by one local hospital. The Community Health Home is a recently introduced service in Italy, mandated by the National Law, to improve the quality of primary care. It includes different professionals within the same community structure, such as general practitioners, specialist physicians, social workers, and other allied health professionals, as well as home care nursing services and family and community nursing services. Specifically, this study directly involves this last group of professionals. Family and community nurses will deliver a structured educational intervention to outpatients with chronic diseases, aiming to reduce unhealthy lifestyles and harmful health behaviors and to promote health in the community. In the Community Health Home setting of the study, two family and community nurses with a Master of Science in primary care work from 7.00 a.m. to 3.00 p.m.

The study has been registered with the number NCT07479810 on https://clinicaltrials.gov/ (accessed on 18 March 2026).

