### 2.4. Intervention

The intervention will be the only manipulated variable, as the nurses involved are the same that would have been leading care for patients and their informal caregivers within the Community Home. Nurses will conduct a therapeutic education program following standard components developed based on multiple frameworks, theories, and evidence, focusing on behavioral changes [27], enhancing engagement and empowerment [28,29], self-care and symptom management [25,26,30], and planning health promotion strategies [31].

Specifically, during the first interview, the nurse will collect the following data.

(a)Socio-demographic status and family network: age, sex, cohabitation status and designated caregiver(s).(b)Patient and caregiver’s priority needs, capturing concerns, difficulties, and expectations with open-ended questions.(c)Clinical condition: vital signs, BMI, diseases and related medications, civil disability status, medical exams, and blood tests.(d)Socio-educational needs, meaning the following:
Lifestyles, combining physical activity, sleeping quality, alcohol consumption, and smoking habits;Self-care skills, using the Patient Activation Measure (PAM) questionnaire [32];Clinical–social frailty, assessing the risk with the Sunfrail questionnaire [33].

Other specific questionnaires will be used whenever concerns or issues are faced. All questionnaires that will be administered are validated in Italian; for each patient, scores will be collected in a specifically designed Excel file. This spreadsheet will serve as electronic documentation, including questionnaires, automated scoring, a summary of active clinical and educational issues, a medication plan, and goals shared with the patient. These elements will be prefilled based on nurses’ data input and finalized manually. The tool will serve as a guide for nurses to deliver the intervention and will become part of the healthcare electronic system. All information will be incorporated into an educational plan, which will be provided to the patient in written form.

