## 3. Limitations and Transparency

This study, like many other pre–post studies, lacks a counterfactual comparison group [42,43], leaving the outcomes exposed to uncontrolled confounders and secular trends. The chosen design aims to assess the pragmatic effectiveness of a nurse-led proactive health intervention in a real-world setting. Health Community Homes are a newly established reality in Italy, designed appropriately to provide the best care for fragile patients. The eligible population and the number of users employed in this setting are nowadays specifically tailored for intercepting and designing new models to care for the elderly with almost one chronic pathology. For these reasons, using a different care facility or primary healthcare professional to provide a comparison is unfeasible. Even if the study employs a double follow-up period and logistic regression to assess confounders, this remains a major limitation for making inferential conclusions. Moreover, the study lacks a justification for the sample size. The selection of this composite endpoint is meaningful in practice, but it does not improve statistical power evaluations. The lack of formally available data makes it impossible to compute a formal sample size, even for the most frequent outcome. Although some evaluations on the cusp of statistical acceptability have been conducted, the researchers prefer not to define this as an a priori power analysis due to its poor reliability. Thereby, they chose to statistically underestimate future results to preserve the study’s informational value [44,45]. Nevertheless, post hoc power analysis would have been subject to excessive variability [46] and would not be helpful overall. Given the risk of type II error, there is no ambition to make inferential conclusions. The focus of this project is on the true value of nursing interventions, so *p* values can be considered less meaningful than other measurements [47]. Taking this into account, the results will cautiously discuss the effect size observed alongside the process evaluations of the intervention, aiming to provide policymakers with useful information on the early introduction of Community Health Homes and Family Nursing.

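### Baseline covariate adjustment cannot remove confounding by time from a one-group before-after contrast, so adjusted estimates should not be presented as confounder control and a pre-specified look-back analysis is needed

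*Protocol article*

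**What the plan says.** Section 2.1 sets the design: "A quasi-experimental pre–post study will be conducted in a Community Health Home". There is no comparison group. Under Section 2.6, primary-outcome events are collected for the same patients over 12 months on each side of enrolment. The self-care and care-experience questionnaires are given at enrolment, 6 months and 12 months.

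For before-after comparisons, Section 2.8 states that "the Wilcoxon signed-rank test and McNemar’s test will be used". Neither test takes covariates. It then adds: "Changes in measures assessed over time will be evaluated using generalized estimating equation (GEE) models, with adjustments for baseline confounders". A sensitivity analysis is something the researchers will consider, and a post hoc one is foreseen if an external shock occurs.

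Section 3 admits that the lack of a comparator leaves the results open to confounding and secular trends, and continues: "Even if the study employs a double follow-up period and logistic regression to assess confounders, this remains a major limitation". It disclaims inferential ambition, citing the risk of type II error. It still intends to discuss the observed effect size for the benefit of policymakers.

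**The concern.** Each patient is his or her own control. Age, sex, diagnoses and frailty as recorded at baseline do not differ between a patient's before and after records, so they cannot confound the period effect. What can confound it changes with time:

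- a secular trend in service use;
- ageing and disease progression;
- regression to the mean, if an acute event prompts the referral. Section 2.2 lists transitional care services among the referral sources, so this is plausible.

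A GEE or logistic regression on baseline covariates does not address any of these. The double follow-up does not either: points at 6 and 12 months lie after enrolment and cannot show where event rates were heading before it.

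An estimate labelled as adjusted for confounders may therefore be read as partly protected when its bias from time is unchanged. Section 3's caution rests on type II error, whereas this bias can inflate the effect and produce false positives. Discussing effect sizes instead of p values does not help, because the effect size is the biased quantity.

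**Working it through.** **Inputs from the article.** Same patients, 12 months before and after (2.6); 100–120 patients and 3-month recruitment (2.2); significance at p < 0.05 (2.8). The article gives no event rate, effect size or share of event-triggered referrals, so these are assumed below. The enrolment target cannot be reproduced, because the article says that it is not a power calculation. The point does not depend on it.

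**Step 1: algebra.** Let t = 0 before and 1 after, and let X_i be a baseline covariate. With complete pairs,

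Σ_i Σ_t (t − ½)(X_i − X̄) = Σ_i (X_i − X̄)(−½ + ½) = 0.

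X is orthogonal to t, so with an identity link the period coefficient is mean(Y_i1 − Y_i0) whether or not X is in the model. The same holds for complete data at enrolment, 6 and 12 months, since X has the same mean at every visit. With a logit link the coefficient moves away from zero through non-collapsibility, which is not control of confounding.

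**Step 2: numerical check.** n = 110, 300 replicates, true intervention effect zero. Assumed logistic model: intercept −1.0, coefficients 1.0 and 0.5 on two standard-normal baseline covariates, patient-level SD 0.8.

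| Scenario | Risk difference, unadjusted / adjusted | Log OR, unadjusted / adjusted |
|---|---|---|
| No trend | 0.001 / 0.001 | 0.005 / 0.006 |
| Secular trend of −0.5 on the logit scale | −0.073 / −0.073 | −0.36 / −0.44 |
| Referral probability 0.60 after an event, 0.15 otherwise | −0.252 / −0.252 | −1.04 / −1.27 |

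In every replicate the two risk differences agreed to within 1e-15.

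**Step 3: range of event-triggered enrolment.** n = 110, 300 replicates, zero effect, 0.7 events per year, gamma shape 1, log-rate coefficient 0.4 for a baseline covariate, binomial GEE.

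| Share triggered by an event | OR, unadjusted / adjusted | Rejected at 0.05 |
|---|---|---|
| 0% | 0.99 / 0.99 | about 5% |
| 10% | 0.83 / 0.83 | 12% |
| 20% | 0.72 / 0.71 | 31% |
| 30% | 0.61 / 0.59 | 61% |

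A separate run of 400 trials at 30% gave OR 0.65 / 0.64 with 49% rejected either way. The exact size depends on the set-up, but adjustment removed none of the bias.

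**Step 4: where adjustment does help.** With no effect and dropout that depends on a baseline covariate, the mean change in a continuous outcome went from −0.152 to +0.014 (independence) or from −0.048 to +0.013 (exchangeable). For a binary outcome the risk difference went from −0.027 to +0.001. The simulation error of the +0.014 is 0.151/√300 = 0.009, so it is compatible with zero.

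**Step 5: can a look-back do better?** No-effect data, n = 110, 0.7 events per year, log-linear GEE on counts with a pre-enrolment trend and a post-enrolment step.

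| Analysis | 30% event-triggered: rate ratio (false positives) | Assumed secular trend: rate ratio (false positives) |
|---|---|---|
| Simple 12-month contrast | 0.76 (53%) | 0.81 (27%) |
| Trend plus step, all pre-enrolment months kept | 0.51–0.64 (76–88%) | not given |
| Trend plus step, 36 months, last 3 left out | 1.02 (10%) | 1.01 (4%) |

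Keeping the months just before enrolment makes matters worse: the referral-triggering spike tilts the fitted trend upward and exaggerates the step.

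**Step 6: calendar time.** Over 36 + 12 = 48 months, time since enrolment has variance 48²/12 = 192. Enrolment dates spread over 3 months add 3²/12 = 0.75. The correlation of calendar time with time since enrolment is √(192/192.75) = 0.998, so a calendar term adds almost nothing.

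**The case against.** The strongest reply is that Section 3 already concedes the main weakness. It admits confounding and secular trends, calls the missing comparator a major limitation even with regression, and disclaims inference. That stands, and it lowers the weight of the point. It does not remove the bias from the effect size that will be reported.

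Second, the GEE sentence may chiefly concern the questionnaires at three time points, with McNemar's test reserved for the primary outcome. That is a fair reading. The algebra in Step 1 covers three visits as well, although the simulations covered two periods only. Missing questionnaires are also where covariate adjustment is most likely to earn its place.

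Several stronger readings are tempting but not supported:

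- **That adjustment is the plan's sole safeguard.** Sensitivity analyses and a double follow-up are also named, though weakly.
- **That adjustment is useless.** Step 4 shows otherwise, although Section 2.7 expects low dropout and primary events come largely from records, so the gain here is probably small.
- **That Section 3's logistic regression contradicts Section 2.8.** A GEE with a logit link is a logistic model, and an article may leave the link unnamed.
- **That "The intervention will be the only manipulated variable" is false because "The Community Health Home is a recently introduced service in Italy".** No opening date for this Home is given, and Section 2.4 explains the phrase by the nurses being the same.
- **That "The region shares an integrated electronic database that provides access to data from all surrounding facilities" contradicts the statement that "using a different care facility or primary healthcare professional to provide a comparison is unfeasible".** Access to data is not permission to use the records of people who have not consented. Such a series also could not reproduce the referral process or the general practitioner's judgement of life expectancy.

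**Conclusion.** The point holds in a limited form. With complete pairs, baseline adjustment cannot remove confounding of this contrast by time, exactly so on the identity scale. On the logit scale it moves the estimate further from zero. Its legitimate uses here are covariate-dependent missingness and conditional estimates.

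The algebra needs no assumption beyond complete data. The sizes do: the false-positive rate of about 5% rising to 49–61% rests on assumed event rates and an assumed 0–30% share of event-triggered referrals. If no referrals are event-driven and there is no trend or progression, there is no such bias.

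This is a change that should be made, of moderate weight because the limitation is disclosed. A better sensitivity analysis is available from a database that the study already uses.

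**What to change.** 1. In Sections 2.8 and 3, describe the adjusted estimates as conditional, or as handling baseline-related missingness, and not as control of confounding.
2. Replace the sensitivity analysis that is only under consideration with a pre-specified one. Extract about 36 months of pre-enrolment emergency department and hospital events from the same regional database. Fit a patient-clustered log-linear GEE to monthly or quarterly counts, with a pre-enrolment trend and a post-enrolment step. Leave out, or model separately, about the last 3 months before enrolment.
3. Report it beside the simple 12-month before-after contrast, noting that it gives a rate ratio and not the proportion with at least one event.
4. Do not add calendar time.

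**Costs.** The interval will be wider and there are more records to extract. The look-back also needs either extra relatedness review under Section 2.6 or the use of all-cause events. The 3-month gap helps only if the triggering events fall inside it, and 10% false positives remained in the referral scenario, so the result still calls for caution. The look-back serves the event outcome only; questionnaires cannot be collected retrospectively.
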